## Methods

### Trial design

This protocol is formulated according to the SPIRIT (Standard Protocol Items: Recommendations for Interventional Trials) statement
^
54
^. It describes a multifactorial mixed-measure design and encompasses three different motor activities. Specifically, the overground walking activity on a wide and a narrow path (ST -wide and ST -narrow) will constitute the core part of the study and will also be examined during a concurrent cognitive color discrimination task (DT -wide and DT -narrow); the cognitive task will additionally be examined in an ST condition for a comprehensive comparison (ST -visual). Second, postural control will be examined in the semi-tandem stance alone (ST -sts) and simultaneously with a cognitive task examining attention (DT -sts). The attention task will also be examined as ST in the seated position (ST -Stroop). Finally, in the seated position, isometric force development activity over time will again be examined alone (ST -is), under dual-task cognitive conditions while performing a series-3 subtraction task (DT -is), with the series-3 subtraction also performed in the absence of the motor task (ST -sub). In each motor activity, namely the overground walking, semi-tandem stance, and isometric contractions, one between-subject factor
*Group* (early PD vs. neurotypical older adults) and within-subject factor
*task complexity* (ST vs. DT) will be considered. In addition, in the walking activity, the second within-subject factor
*walking difficulty* (wide vs. narrow) will be implemented. This leads to a mixed between-within 2 (
*Group*) x 2 (
*task complexity*) study design for the isometric and stance activities and to a mixed between-within 2 (
*Group*) x 2 (
*task complexity*) x 2 (
*walking difficulty*) design for walking activity.
Figure 1 provides an overview of the study structure and timeline, as well as motor activities with ST and DT conditions embedded. We are aware that the direct comparison between the DT conditions of the three motor activities will not be possible due to the use of different cognitive tasks, yet this decision was motivated to avoid extensive learning effects and increasing frustration during the measurement day. A detailed description of the cognitive tasks and their respective stimuli can be found below under “Cognitive task performance”.

**Figure 1. f1:**
[figure not shown]
Graphic depiction of each motor activity, timeline of the procedure, and randomization order. (
**A**) Overground walking will start with a resting-state EEG recording with both eyes closed and opened, followed by a baseline walk, and finally randomized order of ST and DT conditions during overground walking on either wide or narrow lanes with/or visual discrimination task (blue and purple light). (
**B**) Next, the semi-tandem stance will be performed, again using randomization of the ST and DT conditions across participants, while the 30-second segments within each condition will be kept at fixed order. (
**C**) Lastly, during the isometric knee contraction the order of the leg blocks and ST-sub will be randomized, while during each leg block, the ST will always be performed before the DT. Duration of each recording is denoted below the time axis. For a detailed explanation refer to the main text. Abbreviations: ST – single task, DT – dual task, sts – Semi-tandem stance, sub – subtraction or mental arithmetic task.

**
*Ethical approval and confidentiality*.** The study was registered at IRB of Trieste University Hospital – ASUGI, Trieste, Italy (ASUGI protocol number: 106/2021; approved 20.12.2022) and on ClinicalTrials.Gov under code: NCT05477654. The written informed consent for the participants with PD will be obtained by a medical doctor (PM or MC), a movement disorder specialist, employed by the Neurological Clinic of Trieste University Hospital, while for the healthy participants the lead researcher will obtain it. All participant information and data will be stored securely and identified by a coded ID number only to maintain participants’ confidentiality.

**
*Managing adverse effect*.** The protocol and proposed experiments were modified after the pilot trials to minimize the occurrence of factors that led to experiment termination. Specifically, the number of stimuli and the duration of conditions were kept low enough to avoid fatigue but high enough to ensure adequate data quality, while the breaks between tasks/conditions were made sufficiently long. If reasons such as fatigue will nevertheless lead to a request for an interruption, the investigation will be terminated. Similarly, if participants will experience dizziness or will experience adverse effects for other reasons, the examination will be terminated. A physician will be present to ensure physical safety. The experimental day is organized in three experiments, so the recorded data will provide valuable insights despite the number of experiments completed.

### Eligibility criteria

Inclusion criteria for the healthy older participants will be: (1) no diagnosis of cognitive or movement disorder, (2) Montreal Cognitive Assessment (MoCA;
^
55
^) score ≥ 24 points (3) Short Physical Performance Battery (SPPB)
^
56
^ score > 7 points (4) living independently in the community, (5) age range between 50 and 75 years, (6) no color blindness.

Inclusion criteria for the people in the early-stage of PD: (1) diagnosed according to the last International
*Movement Disorder Society Unified Parkinson’s Disease Rating Scale (MDS-UPDRS)* criteria (2015), (2) duration of the disease less than 5 years, (3) positive Dopamine Transporter Scan (DATSCAN), (4) diagnosed akinetic-rigid or mixed phenotype, (5) score of 1 or maximally 2 on the Hoehn and Yahr scale
^
57
^, (6) MoCA score ≥ 24 points, (7) SPPB score > 7 points, (8) age range between 50 and 75 years, (9) no color blindness, (10) living independently in the community.

Exclusion criteria will be (1) advanced stages of PD (Hoehn and Yahr score > 2 points), (2) any acute or untreated chronic diseases, especially of the peripheral and central nervous system, such as heart failure, respiratory failure, severe osteoarthritis, and major psychiatric illness, such as depression, (3) MoCA score < 24 points, (4) severe disabling tremor, (5) recurrent falls, (6) impaired vision that is not corrected with e.g., glasses, (7) SPPB score ≤ 7 points.

### Outcome measures

This protocol focuses on the behavioral, cognitive, motor, and/or kinematic outcomes as well as neurophysiological markers associated with CMI during dual-tasking in healthy aged individuals and people with early PD. The accompanying information regarding the participants' demographics and general health will be treated as supporting outcome and used to control for the confounds.

**
*Principal outcomes*.** The principal outcomes suggested by this protocol will be the DT effects associated with the concurrent execution of overground walking/semi-tandem stance/isometric contraction
*and* a respective secondary cognitive task. The motor task parameters, e.g., the gait parameters using full-body kinematics (step length and width, stride time variability, walking speed), the center of pressure (COP) displacement for the static stance, and deviation of the required force development over time for the isometric contractions, will be investigated in the ST and DT conditions. Additionally, each cognitive task performance will be recorded in the ST condition to allow for the investigation of the DT effect on the cognitive level too. The cognitive ST condition will be performed in a seated position for all cognitive tasks (visual discrimination task, counting of Stroop stimuli, serial-3 subtraction; for description see below). High-density surface electromyography (HD-EMG) and high-density electroencephalography (HD-EEG) will be recorded in all motor activities in both ST and DT conditions. In the overground walking experiment, the DT condition will be created using a visual discrimination task, in the semi-tandem stance experiment the cognitive secondary task will be counting the occurrences of specific visual Stroop stimuli, and finally, in the isometric contraction experiment, the secondary task will encompass mental arithmetic. All tasks include aspects of executive functions. However, to avoid learning effects the task-set up was conducted differently between all conditions. Below are detailed descriptions of the cognitive and motor tasks. 

*Cognitive task performance:*

Contra- vs. Ipsi-Lateral Visual Discrimination Task performance in walking activity: The outcome measures for a visual discrimination task will be response accuracy and response time. The implementation of such a task will allow for the recording of the event-related potentials as well as continuous brain activity. Stimuli of the cognitive task used in the ST and DT walking experiment will vary according to the presentation side (left vs. right), spectral properties (magenta vs. cyan), and presentation-response laterality (ipsi- vs. contra-lateral). DT costs and the associated neural underpinnings will be assessed in the cognitive task as well as in gait parameters.Silent counting of specific Stroop stimulus occurrences in the semi-tandem stance activity: Computerized Stroop task words “Blue” and “Red” will be presented one at a time in either blue or red ink color. Presenting stimuli at a rate of 1/s, participants will have to count the number of specific occurrences, e.g., “Blue” in blue ink, from the four possible options across 30-second intervals. This will be repeated three times, each time focusing on and counting a different color combination of stimuli.Mental arithmetic: Sequential subtracting is typically used as a screening procedure to assess attention/working memory functions. In our study, participants will be asked to quietly perform serial-3 subtraction from a random 3-digit number and verbally indicate the resulting number after a 30-second interval. This will be performed 3 times. The resulting number will be noted and will serve as an indirect measure of success. Standardization and adult norms are available
^
58
^.

*Motor performance:*

For the walking experiment, the full-body kinematics will be captured using 17 inertial Shadow Motion sensors (Motion Workshop, Seattle, WA, USA). To ensure higher precision of body position and alignment correction in space, an additional infra-red based tracker (VivePro, HTC, Taoyuan, TW) surrounded by three base stations will be used. The following gait parameters will be extracted from the feet sensors: walking speed, step length, step width, double support time, and step-to-step variability. The arm swing and hip rotation information will be extracted using the arm and torso sensors. Second, postural control will be measured with a force plate (AMTI HE600600-2 k, Advanced Mechanical Technology, Inc., Watertown, MA, USA). The COP displacement in antero-posterior and medio-lateral directions will be calculated in cm.Lastly in the sitting activity of isometric knee extension, the ST and DT performance will be investigated using the isometric dynamometer (Wise Technologies Ltd., Ljubljana, Slovenia)
*Muscle activity:*

EMG activity will be recorded using two wireless 32-channel probes (MUOVI, OT Bioelettronica S.r.l., Torino, Italy). For walking and semi-tandem stance, 8 x 4 matrix electrodes (10 mm interelectrode distance, HD10MM0804, OT Bioelettronica S.r.l., Torino, Italy) will be attached to bilateral tibialis anterior muscles. For the force tracking task, the electrodes will be attached to the bilateral vastus lateralis muscles. The electrodes and probes will be taped on the skin to minimize motion artifacts.

HD-EMG signals collected during walking and semi-tandem stance will be analyzed in the time and frequency domain using HD-EMG amplitude envelopes techniques to calculate entropy, HD-EMG amplitude barycenter, and spatial differences in HD-EMG signals. HD-EMG signals collected during the isometric force tracking will be decomposed in contributions of single MUs using blind source separation methods
^
59
^ to study individual motor unit firing patterns and early assessment of tremor.

*Brain activity*

EEG activity will be recorded using a mobile 128-electrode wireless system (CGX, Cognionics Inc., San Diego, USA). The electrodes will be mounted onto an elastic cap (easyCAP) and positioned according to the standard 5–10 system
^
60
^. Before recording brain activity during the three motor activities, the continuous resting-state EEG will be recorded at baseline while sitting; for 3 min with both eyes open and eyes closed. After this, the brain activity will be continuously recorded during ST and DT conditions in the overground walking, during postural semi-tandem stance, and finally for the static isometric knee extensions. The investigated event-related markers associated with visual processing in the visual discrimination task during walking activity and attentional task during the semi-tandem stance will be the visual P1, N1, and P2 components over the occipital cortex, and the P3 component over the parietal cortex assessed in both ST and DT conditions. The EEG data during all motor and motor-cognitive tasks will be analyzed by the means of time–frequency spectral analysis. For the first time, the gait-phase spectral modulation
^
61
^ will be assessed during overground walking in PD, to allow for investigation of the movement-related beta band hypersynchrony which is the disease characteristic
^
62
^. The communication between the brain and muscles (i.e., cortico-muscular connectivity) will be assessed by EEG-EMG coherence analysis.

**
*Supporting outcomes*.** The supporting measures will be collected to assess the eligibility criteria and the general health status of cognitive and motor function. These measures will also be used to control for the covarying factors.

*Demographic questionnaire* will collect data on participants' age, sex, ethnicity, body mass and height, leg length, and socio-educational status. Also, their handedness in 10 everyday situations will be asked.

The
*general health questionnaire* will include PD-specific anamnestic questions for the people with PD, while in all participants we will scan for comorbidities, history and ongoing lower limb injuries/surgeries, presence of acute pains, sleeping hours of the last night, and coffee/energy drink intake on the measurement day.

The
*Short Falls-Efficacy-Scale-International* (SFES-I;
^
63–
65
^) is a 7-item questionnaire used to assess the fear of falling associated with the execution of easy and complex physical and social activities. A translated Italian version is available and we will provide a translation for the Slovenian-speaking subsample.

The
*Short Physical Performance Battery* (SPPB;
^
56
^) will assess lower extremity function in the elderly and consists of three sections. First, the ability to perform a Romberg, semi-tandem, and tandem stance. Second, the time of walking a 4-meter track at a comfortable speed is measured. Third, participants must perform 5 sit-to-stand transfers as fast as possible, and time-to-completion is measured. Total SPPB score ranges from 0 (low mobility) to 12 (high mobility; up to 4 points per section) and takes up to 10 min to complete.

The
*New Freezing of gait questionnaire* (N-FOG;
^
66
^) is a 9-item self-reported questionnaire measuring the freezing of gait and walking abilities in people with PD through various scenarios, and the impact of gait freezing on daily activities.

The
*Falls History Questionnaire* (FHS) assesses the falls incidence, location, and consequence in the previous 12 months and is based on the recommendation of the Lamb and colleagues
^
67
^ and Lord and colleagues
^
68
^.

The
*Movement Disorder Society Unified Parkinson’s Disease Rating Scale* (MDS-UPDRS;
^
69
^) is a comprehensive assessment of various aspects of PD including motor and non-motor experience of daily living and the related complications. The evaluation characterizes the extent and burden of the disease.

The
*Montreal Cognitive Assessment* (MoCA;
^
55
^) is a one-page 30-item test developed for screening for mild cognitive impairment. It involves items to assess a range of cognitive domains, including executive functions, visuospatial abilities, language, attention, working memory, abstraction, and orientation to time and place. The duration of the assessment is about 10 min. The validated Italian
^
70
^ and Slovenian versions are available
^
71
^.

The
*Trail Making Test* (TMT;
^
72
^) is a measure of psychomotor speed and attentional set-shifting. It requires the subject to connect 25 encircled numbers randomly arranged on a page in increasing order (Part A), and 25 encircled numbers and letters in alternating and increasing order (Part B) using a pen. Both part A and part B include practice exercises. About 5 to 10 minutes are needed for test administration. The outcome measure of the TMT is the time of completion.

The
*Brief Mood Introspection Scale* (BMIS;
^
73
^) is comprised of 16 emotional/mood adjective or phrase items relating to the present moment and a participant is required to respond using a 4-point Likert scale ranging from definitely do not feel to definitely feel.

The
*Beck’s Depression Inventory* (BDI;
^
74
^) consists of 21 items of depressive symptoms experienced over the past week. Each symptom is described in 4 increasing intensities, and a participant must decide which one best describes their state. Zero to maximum of 3 points are given per item proportionally to the chosen intensity.

The
*Dual-Task Strategy Assessment* is a modified version of the tool used by Wollesen and colleagues
^
75
^ and consists of 6 closed-type questions/statements regarding the employed strategy and allocation of one's attention during DT performance.

The
*NASA Total Load Index* (NASA-TLX;
^
76
^) is a tool assessing subjective workload across 6 subscales: mental, physical, and temporal demand, as well as performance, effort, and frustration. The participant marks the degree of workload on a visual scale, ranging between 1 – 21. The overall score is calculated as a sum or average of the 6 subscales and the questionnaire is applied after each randomized condition in the overground walking activity.

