Participants will be standing on a force plate (AMTI HE600600-2 k, Advanced Mechanical Technology, Inc., Watertown, MA, USA) in a semi-tandem position with their preferred (but always the same) foot in front and with their hands fixed on their hips. Over the 30-second runs in both ST-sts and DT-sts conditions, an average COP sway length (in cm) will be taken as an outcome measure. In DT-sts and ST-Stroop conditions the outcome measure will (also) be the reported number of the required observed Stroop-stimuli. In each of the three 30 sec repetitions, different combinations of Stroop stimuli will have to be attended, (e.g. “Blue” in blue ink, “Red” in red ink, and “Blue” in red ink). We choose silent counting of the Stroop-stimuli occurrences over loud to reduce the talking-related EEG artifacts. To motivate the participants into performing the cognitive task, they are required to report the result at the end of each 30-second trial. During the ST-sts condition, participants will be asked to direct their gaze to a fixation cross presented on the screen at the level of their eyes. 

**
*Isometric knee extension*.** Finally, for the trapezoidal isometric force tracking participants will undergo two 32-second force tracking sessions of knee extension (6 s rising phase, 20 s sustained phase, 6 s decline phase) per both right and left lower limbs in the ST-is motor condition. The participants will be sitting in a knee extension dynamometer (Wise technologies, Ljubljana, Slovenia) equipped with a force sensor and they will be instructed to actively contract their knee extensors to produce force up to 30% of their maximum voluntary contraction (MVC). The force tracking task will be repeated while concurrently performing the secondary serial-3 subtraction task quietly during the DT-is condition for both right and left lower limbs. The serial 3-subtraction task will also be quietly performed in an ST-sub condition for 32 seconds. Each time, a random 3-digit number between 300 and 500 will be selected as a starting point and at the end of the 32 second period, participants will be asked to report the number they had reached. The order of the right and left limbs and the ST-sub will be counterbalanced across the participants, while they will always perform the ST-is before the DT-is with a respective lower limb. The task will consist of 2 rounds of described conditions.

**
*Randomization sequence*.** The randomization sequence will be created via the online

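### Serial subtraction is scored by the raw end number, which mostly reflects the random start and reverses the dual-task cost; Stroop is scored without the true count, and the subtraction set-up is described two ways

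*Protocol article*

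**What the plan says.** The relevant text of the Protocol article is in two places.

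- **Outcome measures, Cognitive task performance (mental arithmetic).** The task is introduced thus: "participants will be asked to quietly perform serial-3 subtraction from a random 3-digit number". Participants then "verbally indicate the resulting number after a 30-second interval. This will be performed 3 times". The score is given as: "The resulting number will be noted and will serve as an indirect measure of success".
- **Procedure, tasks, and stimuli (isometric knee extension).** "Each time, a random 3-digit number between 300 and 500 will be selected as a starting point", and the participant reports the number reached. On duration: "The serial 3-subtraction task will also be quietly performed in an ST-sub condition for 32 seconds". The force-tracking trial that subtraction accompanies in DT-is also lasts 32 s, and the task is run in 2 rounds.
- **Procedure, tasks, and stimuli (semi-tandem stance).** "In DT-sts and ST-Stroop conditions the outcome measure will (also) be the reported number of the required observed Stroop-stimuli". Stimuli appear once per second in 30-second runs, and the target is a different one of four word and ink combinations in each of the three runs.

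The Introduction defines dual-task cost as (DT − ST)/ST. Principal outcomes are the dual-task effects, and each cognitive task is recorded on its own so that the effect can also be studied on the cognitive side.

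**The concern.** A score should move with performance, and in a known direction. The end number of a subtraction run depends on where the run began, and it falls as the participant does better. Nowhere does the article relate it to the start. A reported Stroop count has no direction of merit at all: counting too many and counting too few are both errors, but they move it in opposite directions. Nowhere is it compared with the true count.

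Two of the three cognitive tasks are affected, and both feed principal outcomes. Without a usable cognitive score, a motor dual-task effect in stance or isometric contraction cannot be told apart from a participant who simply neglects the cognitive task. The differing descriptions of the subtraction task add to this, because the number of steps completed depends directly on the time allowed.

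**Working it through.** The article gives no computed figure for these scores. Its only calculated figure, N = 42, does not bear on this point.

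**Inputs from the article:** start between 300 and 500, drawn anew each time; steps of 3; cost = (DT − ST)/ST; 30 Stroop stimuli per run (1 per second for 30 s); four word and ink combinations.

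**Assumed, because the article does not give them:** the number of correct steps k and its SD; a uniform draw of the start; starts independent of k; error-free subtraction.

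**1. What the end number measures.** Reported = start − 3k.

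- Start variance, integers 300 to 500: (201² − 1)/12 = 3366.7, so SD = 58.0.
- Performance variance: 9 × SD(k)².
- Share due to the start = 3366.7 / (3366.7 + 9 × SD(k)²).

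| Assumed SD of k | Performance variance | Share due to start |
|---|---|---|
| 2 | 36 | 98.9% |
| 4 | 144 | 95.9% |
| 6 | 324 | 91.2% |
| 8 | 576 | 85.4% |

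Averaging helps only in part. Dividing the start variance by 2, 3 or 4 trials, with an SD of the mean step count from 3 to 6, leaves a share between 95% and 72%. If the start could be any three-digit number (100 to 999, SD 259.8), the single-trial share exceeds 99% over the same range of SD(k).

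**2. Direction under the cost formula.** Take 12 steps in ST and 9 in DT (assumed).

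- On steps: (9 − 12)/12 = −25%, a loss.
- On the raw number, both starts 400: ST = 400 − 36 = 364 and DT = 400 − 27 = 373, so (373 − 364)/364 = +2.5%.
- On the raw number with independent starts of 300 to 500 (200,000 simulated draws): mean +5%, SD 24 percentage points.

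The sign is reversed, the size is about a tenth of the true cost when the starts are equal, and with independent starts the spread swamps the mean.

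**3. Stroop.** Suppose 8 targets are shown in each of three runs and the reports are 10, 6 and 8 (illustrative). The mean report is 24/3 = 8, which looks perfect. The mean absolute error is (2 + 2 + 0)/3 = 1.33. If the number of targets also varies between runs, that variation is added. Were the four combinations drawn at random, the true count would have mean 30 × 0.25 = 7.5 and SD √(30 × 0.25 × 0.75) = 2.37. It would then explain 96% of the variance of the report at a counting-error SD of 0.5 and 47% at 2.5. The article does not say how the targets are set.

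**4. The two descriptions of subtraction.**

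| | Outcome measures | Procedure, tasks, and stimuli |
|---|---|---|
| Duration | 30 s | 32 s |
| Repeats | 3 | 2 rounds |
| Start | any random 3-digit number | 300 to 500 |

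Two rounds give 2 ST-sub trials and, at one DT-is trial per limb per round, 2 per limb or 4 in all. None of these is 3.

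**The case against.** The best defence is that the article describes data capture, not analysis. It says the number is noted and calls it an indirect measure, which may imply a derived score. A start is chosen for every trial, so start minus end could be computed, and a formula of that kind is often left to a fuller document. Part of this stands: the data may well be recoverable, and a reader should not infer that the raw number is certain to be analysed. But the article does name the measure, it is the end number, and no sentence relates it to the start. By contrast, it scores the visual task by accuracy and response time.

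The Stroop part is weaker. A reader might infer that the reported count mostly reflects the number of targets shown. That needs target counts that vary between runs, which the article does not state. If the count is fixed and equal in every run, it adds no variance, and a consistent tendency to under-count would still show in the raw figure. What remains is that over-counts and under-counts cancel.

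A reader might also infer that dual-task performance gains a false advantage from 32 s against 30 s. No section sets that pairing: the Procedure section gives 32 s for ST-sub and for the force trial, and the 30 s describes the task in general.

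Finally, it is tempting to state a loss of power. The article gives no step counts, spread or expected difference, and a simple comparison of group means would not address the dual-task effect, so no power figure is offered here.

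**Conclusion.** The point holds for the scores as written. For subtraction it is strong. The start accounts for about 85% to 99% of the single-trial variance over assumed step SDs of 8 to 2, and the reversed sign follows from the scoring itself whenever starts are equal. For Stroop the defect is one of kind, since a reported count is not accuracy; its size cannot be given from the article. The conflicts on duration and repeats rest on no assumption. The start range is a looser mismatch, because 300 to 500 lies within the three-digit numbers.

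The scope is limited to the cognitive dual-task effects in stance and isometric contraction. The motor outcomes and the visual discrimination task, and so the walking activity that forms the core of the study, are not touched. The matter should be settled before analysis.

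**What to change.** 1. Record the start number and the number of targets shown for every trial, in ST and DT alike.
2. Score subtraction as (start − reported)/3 per trial, so that higher is better, and flag any difference that is not a multiple of 3.
3. Score Stroop as |reported − presented| per run, divided by the number presented if that varies. State that higher is worse. This error can be zero in ST, where the cost ratio is undefined, so express its dual-task effect as a plain DT − ST difference.
4. Reconcile the Outcome measures and Procedure sections to one duration, one repeat count and one start range, with the same duration in ST-sub and DT-is.

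The cost is a few lines of wording, two scoring definitions and two logged values. The article does not say how the subtraction start is generated or stored. Six participants had already been tested according to Study status, so check now that their start numbers and target counts were kept; a trial without them cannot be rescored.
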